### Secondary hypotheses

*Nursing practice outcomes*: Patients in wards receiving the FLIP will have increased documented VS (complete sets), repeated VS within 30 min of obtaining an abnormal VS, documented nursing scope of practice interventions in response to abnormal vital signs, increased activations for urgent clinical reviews and MET calls in patients fulfilling the criteria. *Clinical Outcomes*: Patients in wards receiving the FLIP will have fewer cardio-respiratory arrests, less unplanned intensive care unit (ICU) admissions, lower unexpected hospital mortality rates and reduced hospital length of stay (HLOS). *Health Economic Outcome*: The cost of implementing the FLIP will be offset by savings from shorter HLOS and reduced ICU admissions. FLIP will represent a cost-effective use of resources.

The study is designed to adhere to the Good Clinical Practice (GCP) Guidelines for national ethics standards and is consistent with the C-RCT CONSORT statement [19] and the CHEERS statement [20], ensuring it meets international ethical and scientific quality standards for reporting clinical trials that include an economic evaluation (see Fig. 1).

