### Sample size

From a medical record review in one of the sites, the rate of adherence to escalation policy after abnormal VS measurement was 53% [6]. Sample size calculations are based on a 50% rate of adherence to escalation as per hospital policy. To detect a 20% improvement in adherence rate in the intervention group immediately following and 6 months post-intervention, 270 documented abnormal VSs per time point per study arm are required. Our sample size has been inflated to allow for a design effect of 1.5, accounting for within-patient autocorrelation and within ward clustering effect. Type I error is set at a 1% significance level accounting for multiple comparisons and study power is set to 90%. For secondary outcomes, we have 80% power to detect an odds ratio of at least 1.8 in post-intervention comparisons for an improved adherence rate in the intervention compared to the control group. For all other secondary outcomes, power calculations have been based on combining immediately following intervention and 6 months post-intervention data. For the unplanned ICU admission rate, a minimum of 0.3% difference (1.2 vs 0.9%); for MET call rate a minimum of 2.3% absolute difference (3 vs 0.7%); and at least 1.6 day (IQR = 20) median absolute difference (12 vs 10.4) for hospital LOS is detectable at 80% power. Due to a low incidence of cardio-respiratory arrests and hospital mortality, a power analysis is based on combining mortality and code blue, resulting in 80% power to detect a minimum 2.3% absolute difference (3 vs 0.7%).

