### Assessments

#### Aims 1 and 2

Outcome data collection will occur across three time points: at baseline prior to implementation, immediately following completion of the intervention (6 months) and 6 months post-intervention (12 months). At each time point, the medical records of all inpatients admitted to study wards will be reviewed by a RA (blinded to group allocation) to determine if abnormal VS were present, and if so, the rates of escalation as per hospital policy, HLOS, unplanned ICU admissions and unexpected inpatient mortality. Data collection days will be randomly selected. RAs will be trained in data entry. Prior to RAs collecting data independently, inter-rater reliability will be evaluated by the project manager who is a registered nurse with specialist intensive care qualifications. Independent data extraction will be conducted until >95% agreement is obtained. The secure data entry system will not allow invalid values; data backup measures will be installed. Costs attributed to FLIP and training will be calculated.

#### Aim 3

Facilitators will complete electronic activity logs; ward communication and policy changes will be collected by RAs electronically. To capture the experience of FLIPs and key stakeholders regarding the intervention and CPG implementation, semi-structured individual and focus group interviews and field observations will be conducted at critical points in the project—before, during and after the intervention. Interviews will be audio-recorded and transcribed verbatim.

All assessments are outlined in Table 1.

**Table 1 Tab1:** Data collection

Aim	Variable/Measure	Instrument	Outcomes	Data collection point
1	Adherence to CPG	eCRF	CPG element compliance: completed VS documentation; repeated VS within 30 min; interventions within scope of practice; CRC and MET activations; escalation as per hospital policy.	Baseline^a^, 6 and 12 months^b^
2	Patient outcomes	eCRF; Hospital clinical databases	Unplanned ICU admissions, cardio-respiratory arrests, limitations of medical treatment orders, HLOS and inpatient mortality.	Baseline^a^, 6 and 12 months^b^
2	Hospital costs	CRF; Hospital clinical costing databases.	Unplanned ICU admissions, HLOS and inpatient mortality; total cost of hospital episode.	Hospital episode^b^
2	Intervention costs	CRF; Staffing salaries	FLIP cost; training frequency	Continuous
3	FLIP dose	eACL	Contact and content of contact.	Continuous

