#### Cost analysis

Analysis of the costs of hospitalisation will be determined at the patient level over the 6-month period for intervention and control wards. All patients admitted to the study wards during the 6-month study period will be included in the analysis of mean total cost, HLOS and ICU LOS for intervention and control wards in each hospital. Only complete admissions will be included (patients admitted to a study ward and discharged from the hospital within the study period); and patients will be analysed based on their admission ward. Mean costs and HLOS for each patient in each ward will be compared to costs and HLOS for patients admitted to the same wards in the 6 months prior to the study period. Difference in difference analyses will be undertaken to compare the mean cost and HLOS difference between pre-intervention and intervention periods, and between intervention and control wards across hospitals. Costs will be attributed to the FLIP intervention based on the additional costs of the implementation process (staff time) over standard in-hospital CPG training.

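### Restricting the cost and HLOS analysis to stays that start and end inside the 6-month window makes inclusion depend on length of stay and, for the hypothesised effect, shrinks the estimated saving by an amount the documents do not fix

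*Protocol article*

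**What the plan says.** All of this is in the protocol article. The Cost analysis section sets the time frame: "Analysis of the costs of hospitalisation will be determined at the patient level over the 6-month period for intervention and control wards". It then defines the population broadly: "All patients admitted to the study wards during the 6-month study period will be included in the analysis of mean total cost, HLOS and ICU" (that is, ICU length of stay). The next sentence narrows it: "Only complete admissions will be included (patients admitted to a study ward and discharged from the hospital within the study period". The comparator is the same wards in the preceding half-year, with mean costs and HLOS "compared to costs and HLOS for patients admitted to the same wards in the 6 months prior to the study period". The estimator is stated as "Difference in difference analyses will be undertaken to compare the mean cost and HLOS difference between pre-intervention and intervention periods", with the two arms contrasted as well. The section does not say whether the complete-admission rule also applies to the earlier 6 months, and it describes no follow-up beyond the end of the window.

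The hypothesis served by this analysis is in Secondary hypotheses: "The cost of implementing the FLIP will be offset by savings from shorter HLOS and reduced ICU admissions". Table 1, under Assessments, lists the hospital cost outcome as "total cost of hospital episode", taken from clinical costing databases.

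The audit cohort is handled differently. Sample/participants has those patients followed for their whole hospital stay, and Data analysis gives their HLOS a median test with a supportive time-to-event analysis.

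**The concern.** A patient enters the cost analysis only if discharged before a fixed calendar date. Someone admitted early in the window is kept unless the stay is very long. Someone admitted in the last weeks is kept only if the stay is short. Averaged over admission dates, the probability of inclusion declines with length of stay, so the sample is selected on an outcome.

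Two things follow. Mean HLOS and mean cost are too low in every group to which the rule is applied. And if the intervention shortens stays, control wards lose more of their long stays than intervention wards do, so the contrast between arms shrinks. Difference in differences removes a bias that is equal in all groups. It does not remove one that depends on the effect being estimated.

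At stake is the cost-offset hypothesis. The cost of facilitation (staff time) is counted separately and the rule does not reduce it, while the saving set against it is estimated too small. A programme that pays for itself could be reported as not doing so.

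**Working it through.** The Cost analysis section gives no sample size, power or expected difference, so there is no figure of its own to reproduce. The check asks what the stated rule does to a known difference.

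**Inputs**
- Window W: 6 months, taken as 182.5 days (Cost analysis).
- HLOS planning values: "at least 1.6 day (IQR = 20) median absolute difference (12 vs 10.4) for hospital LOS is detectable at 80% power" (Sample size).
- Assumed: admissions spread evenly over the window; stay distributions as listed below; the intervention multiplies stays by 10.4/12, the ratio of the planning medians, unless noted.

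**Formula.** A stay of length L is kept with probability w(L) = max(0, 1 - L/W). For example:
- 30 days: 1 - 30/182.5 = 0.84
- 60 days: 1 - 60/182.5 = 0.67
- longer than 182.5 days: 0

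The mean among kept stays is E[L·w(L)] / E[w(L)]. When hardly any stay exceeds W, this is (M - E[L²]/W) / (1 - M/W), where M is the true mean.

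**An example that can be checked by hand** (exponential stays, control mean 6 days, treated mean 6 × 10.4/12 = 5.2; E[L²] = 2M²)
- Control: (6 - 72/182.5) / (1 - 6/182.5) = 5.606/0.967 = 5.80
- Treated: (5.2 - 54.08/182.5) / (1 - 5.2/182.5) = 4.904/0.972 = 5.05
- True difference 0.80, observed 0.75, so 94% is kept and 6% lost.

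**Range over assumptions** (numerical integration)

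| Assumed HLOS, control arm | Dropped, control / treated | True saving (days) | Saving under the rule | Lost |
|---|---|---|---|---|
| Exponential, mean 6 (median about 4) | 3.3% / 2.8% | 0.80 | 0.75 | 6% |
| Log-normal, median 5, IQR 6 | 3.9% / 3.4% | 0.95 | 0.88 | 8% |
| Log-normal, median 8, IQR 10 | 6.4% / 5.6% | 1.56 | 1.33 | 15% |
| Log-normal, median 5, IQR 8 | 4.9% / 4.3% | 1.20 | 0.96 | 20% |
| Exponential, median 12 | 9.5% / 8.2% | 2.31 | 1.84 | 20% |
| Weibull, median 12, IQR 20 | 9.8% / 8.5% | 2.40 | 1.84 | 23% |
| Log-normal, median 12, IQR 20 | 11.9% / 10.4% | 3.01 | 1.72 | 43% |

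In the last row the control mean falls from 22.6 to 16.8 days. A different type of effect, in which the intervention only reduces the share of long stays from 10% to 8% (long stays averaging 40 days), loses 30%.

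**Difference in differences.** With both arms alike in the pre-period, applying the rule to both periods or only to the study period gives the same estimate: -1.72 days against a true -3.01 (log-normal, median 12), and -1.84 against -2.31 (exponential, median 12). The attenuation does not cancel.

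**How much a cohort defined by admission date would recover.** The two 6-month periods are adjacent, so I let a 10% shortening act only on days inside the exposed period (log-normal stays). Share of the true saving recovered:

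| Stays | Current rule | Admission-date cohort, effect stops at month 6 | Admission-date cohort, effect persists |
|---|---|---|---|
| Median 12, sigma 1.125 | 57% | 63% | 81% |
| Median 5, sigma 1.0 | 85% | 88% | 94% |
| Median 4, sigma 0.9 | 92% | 93% | 96% |

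**The case against.** The strongest case against is about size and remedy, and most of it stands.

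A reader might take the Sample size values (median 12, IQR 20) as the protocol's own HLOS for this analysis and conclude that over 40% of the saving is lost. The documents do not support that. Those values appear to describe the audit cohort, meaning patients with abnormal vital signs, whereas the cost analysis covers all ward admissions. The Background says that patients meeting MET criteria had double the hospital length of stay, so the planning values may well be too long for the costed population. The 43% also needs a heavy-tailed log-normal; with the same median, the Weibull and exponential forms lose 23% and 20%.

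A reader might also infer that the rule removes long stays altogether. It does not: a 60-day stay is still kept two times in three. The arms differ in the proportion dropped by at most 1.5 percentage points in the scenarios run.

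The complete-admission rule has a merit too. Applied to both periods, it keeps intervention-exposed days out of the baseline and post-intervention days out of the study period. Following every stay to discharge gives that up, and the gain is small if stays are short or the effect stops at month 6.

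Finally, bias towards zero cannot by itself produce a false claim of savings, and the analysis is secondary. All of this limits the point. None of it makes selection on the outcome sound, or reconciles the rule with the sentence before it.

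**Conclusion.** The point holds for the direction of the bias; the size is uncertain. Inclusion depends on length of stay, the two adjacent sentences of the Cost analysis section define different populations, and difference in differences does not cancel the effect. Mean HLOS and cost are understated, and the saving is biased towards zero for a proportional effect or one on long stays, which is what shorter HLOS and fewer ICU admissions would imply. An effect confined to short stays would not be shrunk.

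The documents contain no HLOS distribution for all ward admissions, so any percentage is an assumption: about 6-20% of the HLOS saving lost for medians of about 4-8 days, and 20-43% if the Sample size values applied. These figures are for HLOS; cost should move the same way in so far as it rises with length of stay. They also assume even admissions and a window of 182.5 days.

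It would be wrong to read this as a flaw in the trial's clinical HLOS comparison. That uses the audit cohorts, followed for the whole stay, and is unaffected. This is a change that should be made to a secondary economic analysis.

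**What to change.** Replace the complete-admission sentence with a cohort defined by admission date: all patients admitted to a study ward within the 6-month study period, and by the same rule within the preceding 6 months, each followed to discharge or death in the hospital costing data. Use a censoring-adjusted mean for stays still open at extraction. Keep the complete-admission analysis as a sensitivity analysis. Flag stays that cross the start or end of the intervention and examine them in a further sensitivity analysis, because they mix exposed and unexposed days.

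The cost is a rewritten sentence or two and a later costing extract. Table 1 already records cost by hospital episode, so a later extract looks feasible, although the documents do not confirm it. The downside is the spill-over of exposed days into the pre-period and of post-intervention days into the study period. In every scenario run the change recovers more of the saving than the present rule does (63-93% if the effect stops at month 6, 81-96% if it persists, against 57-92%), but it does not restore all of it.

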### Setting

Four hospitals in Victoria, Australia, will be the setting for this study. All are acute, major metropolitan teaching hospitals that have more than 400 beds, employ over 1300 nurses and cover both acute and specialist services. Sponsorship for the study was sought from the Executive Directors of Nursing and Chief Executive Officers of each hospital prior to the funding application. Within each hospital, eight to ten wards will be randomly allocated to either intervention or control groups; the intervention will be delivered at ward level. Each ward is considered a cluster for the purpose of analysis. Wards will be eligible for inclusion if they contain 18 or more beds and they receive support from the hospital’s MET. Critical care, emergency, paediatrics, maternity, peri-operative and psychiatric areas will be excluded because they use an alternative response system for patient deterioration.

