### Randomisation

Random 1:1 block randomisation of wards within hospitals to intervention or control groups will be undertaken. A central randomisation service independent of the study will be used with concealment until the intervention is assigned. Assessment days will be randomly selected.

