### Intervention group

The intervention group ward staff will receive the standard implementation of CPGs as described above plus the facilitation intervention for practice improvement (FLIP). FLIP comprises individuals in facilitator roles using facilitation methods and processes in a flexible way to tailor implementation strategies to the local ward context, according to identified barriers and enablers.

There will be two types of internal facilitator roles: hospital facilitators (HFLIP) and ward facilitators (WFLIP). A hospital facilitator will be appointed to cover four or five intervention wards in each of the four hospitals, acting as the overall facilitation lead and coordinator and mentor for the ward facilitators in each hospital. In each intervention ward, two ward facilitators will be appointed to support and enable ward nurses to implement the CPGs into practice (*N* = 36). Each HFLIP will be prepared and supported by an external expert in facilitation (GH). Each HFLIP will work with eight to ten WFLIPs. The facilitation intervention is underpinned by the PARIHS [14, 16] and i-PARIHS [21] frameworks.

Training and a toolkit of methods and techniques will be given to all FLIPs to promote the transfer of CPGs into daily practice. The intervention wards will receive 5 h per week support from the HFLIP for 6 months, reviewing barriers and enablers to implementing CPGs into practice prior to intervention commencement and in discussion with the WFLIPs. The HFLIP will provide face to face interactive education, including small group work, case presentations and role play, as well as review ward specific systems, processes, routines and audit practices in order to align systems of care to enable implementation of CPGs into daily practice. At ward level, the two WFLIPs will work with the HFLIP to audit practice, identify barriers, strategies and goals for improvement. They will provide cover for each other during leave and support ward staff during practice hours, receiving one day per fortnight of protected time for conducting audits, facilitation of ward nurses and meeting with the HFLIP to agree on strategies to improve adherence to guidelines.

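### Cost and HLOS are compared by difference-in-difference although wards are randomised; adjusting for the ward's pre-period mean is a cheap gain in precision

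*Protocol article*

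**What the plan says.** The Cost analysis section of the protocol article covers all complete admissions to study wards over the 6-month study period. Each ward's mean cost and HLOS are "compared to costs and HLOS for patients admitted to the same wards in the 6 months prior to the study period". The between-arm method is named: "Difference in difference analyses will be undertaken to compare the mean cost and HLOS difference between pre-intervention and intervention periods", and then between intervention and control wards across hospitals. ICU length of stay is listed among the outcomes of this analysis, but the pre-period comparison names only cost and HLOS.

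The Randomisation section states: "Random 1:1 block randomisation of wards within hospitals to intervention or control groups will be undertaken". The Setting section gives the number of clusters: "Within each hospital, eight to ten wards will be randomly allocated to either intervention or control groups", in four hospitals.

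The article gives no reason for choosing difference-in-difference, mentions no adjustment for the ward's pre-period value, and gives no pre/post correlation of ward means.

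**The concern.** Difference-in-difference is mainly useful when groups were not randomised and differ systematically at the start. Here any difference between arms in the pre-period arises by chance. The method fixes the coefficient of the ward's pre-period mean at 1, whereas ANCOVA estimates it from the data. If the true slope is below 1, subtracting the whole pre-period mean adds noise that adjustment would avoid.

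The stake is precision. The Secondary hypotheses section expects savings from shorter stay and fewer ICU admissions to offset the cost of the intervention, and this contrast carries that test. There are only about 18 wards per arm, and the data for a better estimator are already being collected.

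**Working it through.** **The plan's own figures.** The article states no sample size, variance or power for the difference-in-difference. Its reproducible sample-size figure is for the primary outcome: 50% against 70%, two-sided 1% and 90% power give 177 per arm, and 177 × 1.5 = 265.5 against the stated 270. That agrees, but it has no bearing on the cost analysis.

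**Inputs.**
- Wards: 4 × 8 = 32 to 4 × 10 = 40 (Setting). The Intervention group section gives 36 ward facilitators at two per ward, so 36 / 2 = 18 intervention wards and about 36 wards in all at 1:1.
- Strata: 4 hospitals (Randomisation).
- Pre-period value: a ward mean, because the patients differ between the two periods (Cost analysis).
- rho, the pre/post correlation of ward means within hospital: not in the document, so a range is used.
- Standard deviations of ward means before and after, s_pre and s_post: not in the document. They are taken as equal unless stated.

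**Large-sample variances**, per ward and on a common scale:
- Difference-in-difference: s_pre² + s_post² − 2·rho·s_pre·s_post
- ANCOVA: s_post²(1 − rho²)
- Difference between them: (s_pre − rho·s_post)², which is never negative.

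With equal standard deviations set to 1, these become 2(1 − rho) and 1 − rho², and the ratio of ANCOVA to difference-in-difference is (1 + rho)/2. A comparison that ignores the pre-period has variance 1. Difference-in-difference is therefore worse than ignoring the pre-period when 2(1 − rho) > 1, that is, when rho < 0.5.

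**Finite-sample cost.** Estimating the slope multiplies the ANCOVA variance by about f = 1 + 1/(ν − 2), with ν = wards − strata − 1. Break-even is where f(1 + rho)/2 = 1, so rho = 2/f − 1.

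| Wards | ν | f | Break-even rho |
|---|---|---|---|
| 32 | 27 | 1.040 | 0.923 |
| 36 | 31 | 1.034 | 0.933 |
| 40 | 35 | 1.030 | 0.941 |

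**Variance ratio, ANCOVA / difference-in-difference, 36 wards, equal standard deviations.** The simulation used hospitals of 8, 8, 10 and 10 wards, normal ward means and 6,000 runs per setting.

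| rho | (1 + rho)/2 | × 1.034 | Simulated |
|---|---|---|---|
| 0.3 | 0.65 | 0.67 | 0.67 |
| 0.5 | 0.75 | 0.78 | 0.78 |
| 0.7 | 0.85 | 0.88 | 0.87 |
| 0.8 | 0.90 | 0.93 | 0.92 |
| 0.9 | 0.95 | 0.98 | 0.97 |
| 0.95 | 0.975 | 1.01 | 1.01 |

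The confidence interval narrows by the square root of the ratio: √0.78 = 0.88, about 12% narrower at rho 0.5, and √0.93 = 0.96, about 4% narrower at rho 0.8.

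**Unequal standard deviations.** When s_pre is close to rho·s_post, the true slope is close to 1 and difference-in-difference is already near its best. At s_pre/s_post = 0.8 and rho = 0.8 the simulated ratio was 1.035. At s_pre/s_post = 1.2 and rho = 0.8 it was 0.71.

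**Bias.** In every simulated setting the mean error of both estimators was within 0.01 of a standard deviation of zero.

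**Given an observed imbalance.** With 18 wards per arm, the standard error of the pre-period difference is √(2/18) = 0.33 ward standard deviations. For an imbalance of that size and equal standard deviations, difference-in-difference is off by (1 − rho) × 0.33: about 0.17 at rho 0.5 and 0.07 at rho 0.8. These errors average to zero over randomisations.

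**The case against.** **High correlation is plausible.** Each pre-period value averages all complete admissions over six months in a ward of at least 18 beds, and ward case mix may be stable. As an illustration resting on assumed figures, 180 admissions per ward and period with a time-stable ward intraclass correlation of 0.05 give rho = 9/9.95, about 0.90; an intraclass correlation of 0.10 gives about 0.95. At those values the two methods are practically equal. This stands, although drift in ward effects or a smaller intraclass correlation would lower rho.

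**Adjustment is not always better.** A reader who knows the large-sample result might infer that adjustment can never lose and has no downside. With 32 to 40 wards that is not so, as the break-even values and the case of s_pre near rho·s_post show. This also stands, with a loss limited to about 3 to 4% of variance.

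**Both estimators are valid.** A reader might infer from regression to the mean that the planned analysis is biased. The document does not support that: allocation is random, and the over-correction exists only conditionally on an observed imbalance.

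**The article is condensed.** Covariates and weights may be set out in a fuller plan. That explains a missing model specification, but this article names the estimator, and that choice can be reviewed as it stands.

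**Conclusion.** The point holds as a cheap improvement, not as an error, bias or contradiction in the plan. For a randomised comparison with pre-period ward data in hand, adjustment is the better default because the trade is asymmetric. With 36 wards and equal standard deviations it saves about 22% of variance at rho 0.5 and 7 to 8% at rho 0.8, and costs at most about 3 to 4% where it loses.

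The size depends on rho and on the ratio of the two standard deviations, neither of which the article gives. If ward means are very stable, the choice hardly matters. The simulation assumed normal ward means. The outcome is secondary, so the priority is low.

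**What to change.** In the Cost analysis section, make the main between-arm analysis of cost and HLOS a ward-level ANCOVA: the ward's intervention-period mean regressed on arm and hospital, with the ward's own pre-period mean as covariate. An equivalent patient-level model that accounts for ward clustering and carries the ward's pre-period mean would also serve. Report the difference-in-difference as a sensitivity analysis. Apply the same model to ICU length of stay only if its pre-period value is also extracted, since the article does not say that it will be.

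For cost and HLOS this changes analysis wording only and needs no new data. The price is up to about 3 to 4% of variance if the pre/post correlation is very high or s_pre is close to rho·s_post. The choice should be fixed before outcome data are seen by arm.
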